## Abstract

**Background:**

In a previous retrospective observational study, a 3-day regimen of oseltamivir as post-exposure prophylaxis (PEP) for preventing transmission of influenza in wards was shown to be comparable to 7- to 10-day regimens provided index cases were immediately separated from close contacts. In order to confirm the efficacy of a 3-day regimen, we started to conduct a prospective, multi-center, single-arm trial.

**Methods:**

This study is a prospective, multi-center, single-arm study designed by the Sectional Meeting of Clinical Study, Japan Infection Prevention and Control Conference for National and Public University Hospitals. Index patients with influenza are prescribed a neuraminidase inhibitor and are discharged immediately or transferred to isolation rooms. The close contacts are given oseltamivir as 75 mg capsules once daily for adults or 2 mg/kg (maximum of 75 mg) once daily for children for 3 days as PEP. All close contacts are monitored for development of influenza for 7 days after starting PEP.

**Discussion:**

A 3-day regimen of oseltamivir as PEP has advantages over 7- to 10-day regimens in terms of costs, medication adherence and adverse effects.

*Trial registration* The Institutional Review Board of Hokkaido University Hospital for Clinical Research, 015-0518, registered on November 11, 2016. UMIN Clinical Trials Registry, UMIN000024458, disclosed on October 31, 2016. https://upload.umin.ac.jp/cgi-open-bin/ctr_e/ctr_view.cgi?recptno=R000027881. Japan Registry of Clinical Trials, jRCTs011180015, disclosed on March 14, 2019. https://jrct.niph.go.jp/latest-detail/jRCTs011180015

## Background

Post-exposure prophylaxis (PEP) using oseltamivir has been shown to be effective for reducing secondary infection of influenza in hospital wards [1]. A retrospective observational study showed that a 3-day regimen of oseltamivir as PEP for preventing transmission of influenza in wards is comparable to 7- to 10-day regimens provided index cases are immediately separated from close contacts [2]. In order to confirm the efficacy of a 3-day regimen of oseltamivir as PEP, we started to conduct a prospective, multi-center, single-arm trial.

## Methods/design

### Aim

The objective of this study is to investigate the efficacy of a 3-day regimen of oseltamivir for PEP of influenza in hospital wards.

### Study setting

This study is a prospective, multi-center, single-arm study designed by the Sectional Meeting of Clinical Study, Japan Infection Prevention and Control Conference for National and Public University Hospitals in Japan. This trial will involve patients from Hokkaido University Hospital, Kagoshima University Hospital, Shinshu University Hospital, Tokyo Medical and Dental University Hospital, Tohoku University Hospital, Kobe University Hospital, Chiba University Hospital, Osaka City University Hospital, Tottori University Hospital and Shimane University Hospital in Japan.

### Endpoints

The primary endpoint is the incidence of influenza for 7 days after starting PEP using oseltamivir by use of a 3-day regimen. The development of influenza is defined as development of influenza-like symptoms (e.g., fever, cough and runny nose) with a positive immunochromatographic test (ICT). The secondary endpoints are the associations of the incidence of influenza for 7 days after starting PEP using oseltamivir by use of a 3-day regimen with age, sex, influenza vaccination and underlying conditions of the patients because of the possibility of development of influenza in elderly patients, unvaccinated patients and immunocompromised patients even if they are prescribed oseltamivir.

### Study design

The index patients with influenza are prescribed a neuraminidase inhibitor and are isolated from close contacts [2]. Close contacts who fulfill all of the criteria described in “Eligibility and exclusion” are given oseltamivir [75 mg capsules once daily for adults or 2 mg/kg (maximum of 75 mg) once daily for children] for 3 days as PEP. Since PEP with anti-influenza agents is widely practiced in Japan for both healthcare workers and patients, even for those who have already received vaccination, it is difficult to conduct a randomized controlled trial with comparison of a 3-day regimen of oseltamivir and a placebo control. The results of previous studies are destined to be used as historical controls [1–4].

### Eligibility and exclusion

Eligible participants are (1) patients over 1 year of age, (2) patients sharing a room with index patients with influenza who are separated immediately (ex. by discharge or transferring to isolation rooms), (3) patients in whom administration of oseltamivir as PEP is started within 48 h after onset of fever of the index patients and (4) patients for whom written informed consent to participate in the study is obtained by the physicians participating in this study, from the patients themselves or from proxies. The following patients are not eligible for participation in this study: (1) patients with impairment of renal function (creatinine clearance ≤ 30 ml/min) and (2) patients between 10 and 19 years of age, because the Japanese Ministry of Health, Labor and Welfare issued a warning against the use of oseltamivir in teenagers, except for those at high risks, after reports of two suicides by teenagers shortly after ingestion of oseltamivir in March 2007 [5].

### Study intervention and timeline of the study

The following information will be obtained from each patient’s record at the time of enrolment: (1) body temperature, respiratory symptoms (e.g., cough and runny nose) and results of an immunochromatographic test (ICT) of influenza in index patients, (2) clinical history including age, sex, body weight, influenza vaccination, past infection with influenza, underlying disease and medical history, and results of laboratory tests including hemoglobin, white blood count, aspartate aminotransferase (AST), alanine aminotransferase (ALT) and creatinine for the close contacts. Eligible participants for whom administration of oseltamivir is started as PEP are monitored for influenza-like symptoms (fever and respiratory symptoms) for 7 days (Table 1). If the eligible patients have influenza-like symptoms with a positive immunochromatographic test (ICT), they are regarded as having developed influenza. Information on adverse events will be obtained regardless of their grade of severity. This trial was declared and registered on November 11, 2016 (see “Trial status”).

**Table 1 Tab1:** Schedule of data collection

	Before PEP^a^	Observation period						
		Day 1	Day 2	Day 3	Day 4	Day 5	Day 6	Day 7
Informed consent	X							
Clinical assessment^b^	X							
Laboratory test^c^	X							
PEP^a^		X	X	X				
Fever		X	X	X	X	X	X	X
Respiratory symptoms^d^		X	X	X	X	X	X	X
Immunochromatographic testing^e^		X	X	X	X	X	X	X
Adverse events		X	X	X	X	X	X	X

^a^Post-exposure prophylaxis

^b^Clinical assessment: history including age, sex, body weight, influenza vaccination, past infection with influenza, underlying disease and medical history

^c^Laboratory test: hemoglobin, white blood count, aspartate aminotransferase (AST), alanine aminotransferase (ALT) and creatinine

^d^Respiratory symptoms: cough or sneezing

^e^If the close contacts with index patients with influenza have fever or respiratory symptoms within 7 days after PEP, immunochromatographic testing of influenza will be carried out

### Sample size

In our previous study [2], we prophylactically administered oseltamivir for 3 days to 212 patients, and only 2 (0.9%) of the patients developed influenza. In preceding clinical trials [1, 3, 4], the proportion of patients with influenza infection in the placebo group was about 7%. In this study, it is assumed that the proportion of patients with influenza will be lower than that in preceding studies due to the different study environments. Based on the idea of non-inferiority margin [6], the clinically meaningful margin is set to be 50% of pre-existing risk difference (δ = 7 − 1 = 6%). Therefore, the non-inferiority margin of our study is set to be 3%. From the above argument, we assumed that the proportions of patients with influenza infection are 1% in this study (3-day regimen) and 4% in the null reference. Since the incidence of influenza in a hospital is relatively low and it is possible to confirm the presence or absence of influenza in a short period of time, a binomial distribution was assumed for the incidence. Using the binominal exact test statistic, the expected sample size was calculated to be 253 for detection of a 3% risk difference to achieve a power of 80% at a one-sided significance level of 2.5%. Considering the dropout rate as 10%, the final sample size became 279.

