### Statistical analysis

For primary outcome assessment, a binomial (exact) test is performed to test the risk difference of 3% (proportions of patients with influenza infection being 4% for the null reference and 1% for the proposed regimen) at the one-sided significance level of 2.5%. Descriptive statistics are calculated for the secondary outcomes. All analyses are performed using SAS Version 9.4 (Cary, NC: SAS Institute Inc).

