### Trial status

This trial was declared and registered on November 11, 2016. Recruitment into the trial started on November 11, 2016 and will end in March 2024 or until a total of 279 participants have been recruited. Between November 2016 and May 2020, 68 patients were enrolled. Among them, 3 patients developed influenza after starting PEP using oseltamivir by use of a 3-day regimen.

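### The 10% dropout allowance is miscalculated: 253 evaluable needs 282 enrolled, not 279. The power cost is 75.6% at exactly 10% dropout but about 81% on average, so this is a minor-to-moderate correction.

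*Protocol article*

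**What the plan says.** The Sample size section of the protocol article sets the planning rates: "the proportions of patients with influenza infection are 1% in this study (3-day regimen) and 4% in the null reference". With the exact binomial test, "the expected sample size was calculated to be 253 for detection of a 3% risk difference to achieve a power of 80" per cent at one-sided 2.5%. The next sentence makes the dropout allowance: "Considering the dropout rate as 10%, the final sample size became 279". The inflation formula is not printed.

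The Statistical analysis section names the same exact binomial test against 4% for the primary outcome, "at the one-sided significance level of 2.5" per cent. The Trial status section uses the inflated figure as the recruitment ceiling: recruitment "will end in March 2024 or until a total of 279 participants have been recruited".

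**The concern.** A dropout allowance should leave the required number after the stated loss. Taking 10% off 279 leaves 251, which is below the 253 that the preceding sentence requires. Multiplying by 1.1 instead of dividing by 0.9 is a common slip and in most trials changes almost nothing. Here it needs checking because the primary test is an exact test on very few expected events. Its critical value is a whole number of cases, so power moves in jumps as the evaluable number changes. If 253 sits on such a jump, a shortfall of two participants can change how many cases still count as success, and power with it. Trial status reports 3 cases among the first 68 enrolled, so whether success means at most 3 or at most 4 cases has practical weight.

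**Working it through.** **Inputs (protocol article, Sample size and Statistical analysis):** null rate p0 = 0.04; assumed rate p1 = 0.01; one-sided level 0.025; target power 80%; single-arm exact binomial test; 253 required; 10% dropout; 279 enrolled.

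**Rule.** For n evaluable participants, the critical count c is the largest integer with P(X ≤ c | n, 0.04) ≤ 0.025. Power is P(X ≤ c | n, 0.01).

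**Step 1: reproduce 253.**

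| n | P(X ≤ 4 given 4%) | c | exact level | power at 1% |
|---|---|---|---|---|
| 251 | 0.0263 | 3 | 0.0090 | 75.6% |
| 252 | 0.0256 | 3 | 0.0088 | 75.4% |
| 253 | 0.0249 | 4 | 0.0249 | 88.8% |
| 279 | 0.0123 | 4 | 0.0123 | 85.0% |
| 282 | 0.0113 | 4 | 0.0113 | 84.5% |

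The critical count is 3 for n = 217 to 252 and 4 for n = 253 to 288. Power is at least 80% for n = 217 to 230, below 80% for n = 231 to 252, and at least 80% for every n from 253 up to 299, the end of the range examined. So 253 reproduces as the smallest n from which power stays at or above 80%. It is also the first n at which 4 cases are significant.

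**Step 2: reproduce 279.**
- 253 × 1.1 = 278.3, rounded up to 279. This matches the printed figure.
- 253 / 0.9 = 281.1, rounded up to 282. This does not.

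**Step 3: apply the stated loss.**
- 279 × 0.9 = 251.1, so 251 evaluable: at most 3 cases, power 75.6%.
- 282 × 0.9 = 253.8, so at least 253 evaluable: at most 4 cases, power about 88.8%.
- With 279 enrolled, at most 279 − 253 = 26 can be lost before n falls below 253; 26 / 279 = 9.3%.

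**Step 4: let dropout vary.** The number lost will not be exactly 10%. Taking the evaluable number as Binomial(N, 0.9) and averaging the exact power over it:

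| enrolled N | P(evaluable < 253) | average power |
|---|---|---|
| 279 | 0.60 | 81.1% |
| 282 | 0.39 | 83.5% |

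The average for 279 stays near 80% because power is about 76% when the evaluable number falls below 253 and about 88% when it does not: 0.60 × 0.763 + 0.40 × 0.884 ≈ 0.81.

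**The case against.** The strongest reply is that 75.6% is a worst point on a sawtooth. It applies at or very near 251 evaluable. At 9.3% dropout or less, at least 253 remain and power is 85% to 89%. Averaged over random dropout around 10%, power at 279 is 81.1%, which meets the 80% target. Raising enrolment to 282 adds about 2.4 points of average power (83.5 − 81.1) and still leaves fewer than 253 evaluable about 39% of the time. The test holds its level at every n. Recruitment is also slow: 68 enrolled between November 2016 and May 2020, with an end date of March 2024, so a ceiling of 279 or 282 may never bind. All of this stands, and it limits the weight of the point.

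A second reply is that the article never says what the 10% is a share of, so 279 could mean simply adding 10%. This does not rescue the figure. A dropout rate is a share of those enrolled, and 279 less 10% is below the 253 the same section requires, whichever formula was used.

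A reader might go further and infer that the trial fails to deliver its stated 80% power, or that the validity of its primary test is in doubt. The documents do not support either. The power loss is conditional on the evaluable number landing just below 253, and the exact level there is 0.0090, well inside 2.5%. Nor does the success rule change: the Statistical analysis section fixes the cut-off for any n, and a lower count at smaller n is how an exact test behaves.

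**Conclusion.** The enrolled figure is wrong as printed. It should be 282 under the plan's own 253 and 10%. The error is 3 participants, about 1%. At exactly 10% dropout it puts the trial just below the step at 253, with at most 3 cases allowed instead of 4 and power of 75.6% instead of 88.8%, against a stated target of 80%. With dropout varying randomly around 10%, average power is about 81%, and the type I error is controlled throughout. This is a minor-to-moderate correction.

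The conclusion rests on three assumptions: that dropouts leave the primary analysis, which is what inflating for them implies; that the planning rates of 1% and 4% are taken as given; and, for the average figures, that losses are independent with probability 10%. That 279 came from multiplying by 1.1 is inferred from the arithmetic, but the shortfall does not depend on it.

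**What to change.** Either of two changes is enough.

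1. Keep 279 and restate what it delivers in Sample size: with 10% dropout about 251 participants are evaluable, success requires at most 3 cases, and power is about 76% (about 81% averaged over random dropout). This costs one sentence and a slightly less favourable power figure.
2. Correct the enrolled figure to 282 (253 / 0.9) in both Sample size and Trial status. This costs 3 more participants. It does not guarantee 253 evaluable.

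Listing the critical count by evaluable number (217 to 252: at most 3 cases; 253 to 288: at most 4) would be a useful clarification but is optional, since the named test and level already determine it. Because cases are being counted as the trial runs, a change made before recruitment closes avoids any appearance that the final number was chosen around the step.

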### Statistical analysis

For primary outcome assessment, a binomial (exact) test is performed to test the risk difference of 3% (proportions of patients with influenza infection being 4% for the null reference and 1% for the proposed regimen) at the one-sided significance level of 2.5%. Descriptive statistics are calculated for the secondary outcomes. All analyses are performed using SAS Version 9.4 (Cary, NC: SAS Institute Inc).

### Ethics

The trial will be conducted under ICH E6 (R2) and Ethical Guidelines for Medical and Health Research Involving Human Subjects (Japan). The trial will adhere to the Clinical Trials Act (Japan) from April 1, 2019. Recruitment of participants can start following approval by the IRB of each hospital. The recruitment in Shinshu University Hospital and Kobe University Hospital will be discontinued from April 1, 2019 onward.

### Data quality assurance

The investigators will be responsible for implementing and maintaining quality assurance and quality control systems in accordance with written standard operating procedures. Centralized monitoring will be implemented in accordance with the manual prepared prior to the beginning of the trial.

### Data security

Confidential patient information is kept secure by the rules of medical confidentiality and is treated according to the Act on the Protection of Personal Information in Japan.

### Safety

Participants will be free to withdraw at any time from participation. An investigator may decide to terminate participation in the study if a participant meets an exclusion criterion (either newly developed or previously recognized) that precludes further participation.

### Adverse event (AE)

An adverse event (AE) will be managed according to the FDA’s guidance [7]. All severe adverse event (SAE) information will be reported to the IRB and must be shared with all investigators participating in the study.

## Discussion

The effectiveness of PEP using oseltamivir by use of 7 to 10-day regimens has been shown by several studies [1, 3, 4, 8]. In a previous retrospective observational study conducted from the 2005/06 to 2014/05 influenza seasons, a 3-day regimen of oseltamivir as PEP for preventing transmission of influenza in wards was shown to be comparable to 7- to 10-day regimens of oseltamivir provided index cases were immediately separated from close contacts [2]. A 3-day regimen of oseltamivir as PEP has advantages over 7- to 10-day regimens as regards costs, medication adherence and adverse effects [9].

The incidence rate of influenza within a hospital and the expected incidence rate for the proposed regimen are both low; thus, for the detection of a small difference, the required sample size would become large to achieve nominal statistical power. In order to confirm the efficacy of a 3-day regimen of oseltamivir for PEP of influenza in wards, we started to conduct a prospective, multi-center, single-arm trial of a 3-day regimen of oseltamivir for PEP.

### Trial status

This trial was declared and registered on November 11, 2016. Recruitment into the trial started on November 11, 2016 and will end in March 2024 or until a total of 279 participants have been recruited. Between November 2016 and May 2020, 68 patients were enrolled. Among them, 3 patients developed influenza after starting PEP using oseltamivir by use of a 3-day regimen.

## Data Availability

Not applicable.

## Abbreviations

PEP: Post-exposure prophylaxis
ICH: International Conference on Harmonisation
AE: Adverse event
SAE: Serious adverse event
